## 13 1.0 Study Summary

14

|                                                           |                                                                                                                                                                                                                                                                                                                                                                                                                                                                                                                                                                                                                                                                                                                                                                                                                                                                                                                                                                                                                                                                                                  |
|-----------------------------------------------------------|--------------------------------------------------------------------------------------------------------------------------------------------------------------------------------------------------------------------------------------------------------------------------------------------------------------------------------------------------------------------------------------------------------------------------------------------------------------------------------------------------------------------------------------------------------------------------------------------------------------------------------------------------------------------------------------------------------------------------------------------------------------------------------------------------------------------------------------------------------------------------------------------------------------------------------------------------------------------------------------------------------------------------------------------------------------------------------------------------|
| Study Title                                        | Evaluating FDA's Proposed Patient Medication Information Handout: A Randomized Trial Measuring Perceived Usefulness and Comprehension                                                                                                                                                                                                                                                                                                                                                                                                                                                                                                                                                                                                                                                                                                                                                                                                                                                                                                                                                            |
| Study Design                                       | 
Allocation: Randomized
 
Interventional Model: Parallel Assignment
 
Interventional Model Description: Participants will be randomized to receive either the one-page FDA-template PMI (FDA PMI), a modified template, which added quantitative information about drug risks and benefits (Decision Critical PMI), or the existing drug information insert (Vendor PMI – available at: https://www.fda.gov/media/164654/download).
 
Participants will complete the same survey questions measuring usefulness, comprehension of the information, and perceived strength of the regulatory evidence.
 
Masking: Single (Investigator)
                                                                                                                                                                                                                                                                                                                                             |
| Primary Objective                                  | To compare FDA's new PMI template ( FDA PMI ) to 1) the current drug information insert ( Vendor PMI ) and 2) a decision science-informed revision ( Decision Critical PMI )                                                                                                                                                                                                                                                                                                                                                                                                                                                                                                                                                                                                                                                                                                                                                                                                                                                                                                |
| Research Intervention(s)/ Investigational Agent(s) | 
FDA template PMI
 
Intervention is an information format viewed by participants. The patient medication information format was designed according to a proposed FDA template, which provides information about safe and effective use of a medication. No drug or device is included as part of this intervention.
 
Decision Critical PMI
 
Intervention is an information format viewed by participants. The patient medication information format was designed according to the proposed FDA template and modified, according to decision science principles, to include quantitative risk and benefit information, which provides information about safe and effective use of a medication. No drug or device is included as part of this intervention.
 
Vendor PMI (Control)
 
The intervention is an information format viewed by participants. This patient medication information format is the current patient medication information that is included with the drug. No drug or device is included as part of this intervention.
 |
| Study Population                                   | US adults of reproductive age (18-45) who are assigned female at birth                                                                                                                                                                                                                                                                                                                                                                                                                                                                                                                                                                                                                                                                                                                                                                                                                                                                                                                                                                                                                           |
| Sample Size                                        | 330                                                                                                                                                                                                                                                                                                                                                                                                                                                                                                                                                                                                                                                                                                                                                                                                                                                                                                                                                                                                                                                                                              |

## Evaluating FDA's Proposed Patient Medication Information Handout

|                                                   |                                                                                                                                                                            |
|---------------------------------------------------|----------------------------------------------------------------------------------------------------------------------------------------------------------------------------|
| Study Duration for individual participants | Participation is not anticipated to exceed 30 minutes                                                                                                                      |
| Study Specific Abbreviations/ Definitions  | BRF: Benefit-Risk Framework
FDA: Food and Drug Administration
PMI: Prescription Medication Information
RCT: Randomized clinical trial |

15  
16  
17

## 2.0 Background

In Fall 2023, FDA proposed amending its current prescription drug labeling regulations to facilitate patient decision-making. It would require drug companies to provide patient medication information (PMI) in a new template. FDA proposed a one-page document that highlights the “essential information that patients need to know about the prescription drug product, including basic directions on how to use the product safely and effectively.” When evaluating drugs for approval, FDA uses a Benefit-Risk Framework (BRF). The BRF considers risks, benefits, and alternatives for a drug. FDA references the BRF as guiding development of the new PMI, which largely aligns with the BRF. However, the current proposal does not contain information regarding a drug’s *benefit*, thereby omitting critical information for patients’ decision-making. FDA’s proposal also does not include any quantitative estimates of the medication’s risks or benefits, which decision science research has demonstrated that people utilize in their decision-making process. Additionally, the proposal does not require user testing of PMIs.

We aim to address these issues by (a) extending the proposed PMI to include benefit information and quantitative information about safety and effectiveness and (b) demonstrating a simple procedure for user testing. Using Mifeprex (generic: Mifepristone) as a case study, we demonstrate the procedure with a medication that is FDA-approved, safe, and effective medication for abortion and miscarriage management up to 10 weeks’ gestation.

## 3.0 Objectives

The primary objective of this study is to evaluate the effectiveness of prototypes displaying patient medical information (PMI) for prescription medications. Prototypes tested will display information for mifepristone, a medical abortion medication. We are interested in how the display of prescription medication information affects individuals’ comprehension and the best format to display this information.

The primary research questions are the following:

- How does the proposed one-page *FDA PMI* compare with the current drug information insert (*Vendor PMI*) in terms of usefulness and comprehension?
- How does the proposed one-page *FDA PMI* compare with a revision adding quantified risk/benefit information (*Decision Critical PMI*)?

## 4.0 Setting/Participants

Individuals will be recruited using the Prolific online survey recruitment platform, which pre-screens all individuals for pre-specific study eligibility criteria from a

nationally representative panel of research survey volunteers. Recruitment text is shown in Appendix 1. Participants who meet pre-specified eligibility criteria will be shown the recruitment text and can choose whether to continue to the survey and view the informed consent information. The Qualtrics survey platform will be used to administer the survey, where participants will be randomized, using the embedded Qualtrics randomization function, to view one of the 3 information formats in a 1:1:1 ratio. Participants will be paid \$10 for completion of a survey that should take no longer than 30 minutes.

## 5.0 Inclusion and Exclusion Criteria

To be included in this study participants must self-identify as being biological capability of pregnancy but will not be excluded due to gender identity. Participants under age 18 or above age 45 will be excluded. Only those located within the US will be included. This information is collected by the Prolific platform and only individuals meeting these criteria will be shown the study recruitment materials.

The survey will include one attention check question (Appendix 2). Individuals who fail them will not be eligible for survey participation. Additionally, this study aims for 30% of the study sample to be comprised of individuals who are at/below high school/GED education level. Additional demographic information including gender, race, ethnicity, and residential zip code will be asked to characterize the participant sample but will not be considered as inclusion/exclusion criteria. Eligibility demographics will also be queried at the completion of the survey (age, sex) to confirm eligibility.

## 6.0 Analyses and Data Management

**Intervention.** Participants will be assigned randomly in parallel to one of the three following PMI formats:

### *FDA PMI*

Patient medication information designed according to FDA template specifications. This template provides information about safe and effective use of a medication. No drug or device is included as part of this intervention.

### *Decision Critical PMI*

Patient medication information designed according to FDA template and modified, according to decision science principles, to include quantified risk/benefit information. No drug or device is included as part of this intervention.

### *Vendor PMI (control)*

This patient medication information format is the current standard of care patient medication information that is included with the drug. No drug or device is included as part of this intervention.

**Primary outcome.** Participants responses will be evaluated in the following domains:

Usefulness of Information

*Readability*

- Single question with a 5-point Likert scale response for "How easy or difficult was it to read the medication information guide about Mifeprex?" Minimum score is 1; Maximum score is 5. A higher score represents higher perceived readability.

*Supports Decision Making*

- Single question with a 5-point Likert scale response for "For someone who had not yet decided to use Mifeprex, how useful would the medication information guide be in helping them to make that decision?" Minimum score is 1. Maximum score is 5. A higher score represents higher perceived usefulness.

*Supports Proper Use*

- Single question with a 5-point Likert scale response for "If someone had decided to use Mifeprex, how useful would the medication information guide about [drug] be in helping them use the drug properly? " Minimum score is 1. Maximum score is 5. A higher score represents higher perceived usefulness.

Comprehension

- 10 newly constructed questions designed to measure the comprehension of the following information from the medication information guide: 1) Analysis of condition (1 question) 2) Risks (3 questions) 3) Risk Management (3 questions), and 5) Benefits (3 questions). Participants can score from 0-10 with 10 representing full comprehension of the information and 0 representing no comprehension of the information. Comprehension questions will be divided into two scores: *Knowledge Common to All PMIs* (Appendix 3 #1, 2, 6-10) and *Quantified Risk/Benefit Knowledge* (Appendix 3 #3-5).

Perceptions of Regulatory Data

*Strength of Evidence*

- Single question with a 5-point Likert scale response for "In your opinion, how strong is the *scientific evidence* that

134 Mifeprex, when taken correctly, helps patients end an early  
135 pregnancy?" Minimum score is 1; Maximum score is 5. A  
136 higher score represents stronger perceived evidence.

137 *Drug Safety*

- 138 ○ Single question with a 5-point Likert scale response for "In  
139 your opinion, how *safe* is Mifeprex, when taken correctly, for  
140 ending an early pregnancy?" Minimum score is 1. Maximum  
141 score is 5. A higher score represents higher perceived safety.

142 *Drug Effectiveness*

- 143 ○ Single question with a 5-point Likert scale response for "In  
144 your opinion, how *effective* is Mifeprex, when taken correctly,  
145 for ending an early pregnancy?" Minimum score is 1.  
146 Maximum score is 5. A higher score represents higher  
147 perceived effectiveness.

148 The full survey questionnaire can be found in Appendix 3.

149 **Survey pretest.** The PMI designs and survey questions were pretested  
150 with a convenience sample of the research team's social network  
151 (colleagues, family, friends). After revision, in response to this feedback, a  
152 pilot study of 30 participants was recruited on the Prolific platform to test  
153 the revised survey and inform power calculations for the study, which will  
154 use the same platform. No one who participated in the pilot will be eligible  
155 for inclusion in the main study.

156 **Analyses.** We will compare outcomes across the different PMI formats,  
157 first with a Kruskal-Wallis test for mean differences, followed by a Mann-  
158 Whitney test for pairwise comparisons. We will use a Bonferroni-  
159 correction to account for multiple comparisons,  $\alpha = .01$  for ordinal  
160 variables. Additionally, we will conduct sensitivity analyses to assess  
161 changes in the primary outcomes (usefulness and comprehension): (1)  
162 including individuals who are excluded due to completing the survey too  
163 quickly ( $< 6.97$  minutes, which represents the 10th percentile of  
164 completion time from the pilot data collection) and (2) excluding  
165 individuals who report not believing in using abortion medication under  
166 any circumstance (Appendix 3 #14), as they are unlikely to belong to the  
167 potential user population. To assess the distribution of the individuals  
168 participating in this study, optional questions regarding demographic  
169 information and the study participant's previous exposure Mifeprex (i.e.,  
170 *Have you or someone you care about ever used the drug described in the*  
171 *medication guide?*) will be asked at the end of the survey. We will assess  
172 whether the Qualtrics randomization function was successful by checking  
173 the distribution of participants among the PMI groups. We should expect  
174 to see even distribution in group allocation, and approximately 30% of

175 each group to have at most a high school education. Other characteristics  
176 should be similarly distributed across study groups.

177 Based on response variance in our pilot study, a sample size of 100  
178 participants per condition will yield statistical power with at least 85%  
179 chance of detecting a 0.5-point difference in comprehension (with a  
180 minimum score of 0 and maximum score of 7) between the *FDA PMI* and  
181 *Vendor PMI* group, assuming a two-sided  $\alpha = .05$ .

182 We hypothesize that the *FDA PMI* and *Decision Critical PMI* will be  
183 perceived as more readable and demonstrate greater comprehension than  
184 the *Vendor PMI*, as these formats are designed with readability and  
185 comprehension in mind. Additionally, we anticipate the *Decision Critical*  
186 *PMI* will be rated as more useful in supporting decision-making than the  
187 other two PMI formats. We do not anticipate differences in supporting  
188 proper drug use since supporting use is the primary goal of the *Vendor* and  
189 *FDA PMI* formats.

190 All analyses will be conducted using R Statistical Software (v4.3.2).

191 **Ethical considerations.** This study received expedited review and  
192 approval by Carnegie Mellon University's Institutional Review Board  
193 (STUDY2023\_00000449). The study protocol was registered on  
194 ClinicalTrials.gov (NCT06320808) and followed the Consolidated  
195 Standards of Reporting Trials (CONSORT) guidelines.

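### The Bonferroni alpha of .01 fits five primary measures, but the protocol lists eight as primary, labels the .01 for ordinal variables, and powers comprehension at .05

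*Protocol*

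**What the plan says.** All of this is in Section 6.0 of the protocol.

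- **Primary outcome paragraph.** It opens with "Participants responses will be evaluated in the following domains" and lists three domains. Usefulness has three single items. Comprehension has ten questions, and "Comprehension questions will be divided into two scores" (seven questions and three questions). The third domain, "Perceptions of Regulatory Data", has three single items. That makes 3 + 2 + 3 = 8 measures.
- **Analyses paragraph, tests.** Outcomes are compared "first with a Kruskal-Wallis test for mean differences, followed by a Mann"-Whitney test for pairs. The text does not say whether the pairwise tests depend on the Kruskal-Wallis result.
- **Analyses paragraph, multiplicity.** "We will use a Bonferroni" correction, with "\alpha = .01$ for ordinal" variables. No count of tests is given, and no separate level for any other kind of variable.
- **Analyses paragraph, sensitivity analyses.** These are to assess "changes in the primary outcomes (usefulness and comprehension"), which is 3 + 2 = 5 measures.
- **Power statement.** It claims at least 85% power with 100 per condition for a 0.5-point difference on the 0 to 7 comprehension score, FDA PMI against Vendor PMI, at two-sided .05.

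**The concern.** A Bonferroni level has meaning only together with the set of tests it divides .05 across. Here the set has to be inferred, and the clues disagree. The sensitivity text points to five measures, the primary heading to eight, the ordinal label most directly to the six Likert items, and the power statement to a level of .05 for comprehension.

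Two things are at stake. First, the threshold for a claim such as greater comprehension, which is one of the stated hypotheses, could be chosen after the data are seen. Second, if .01 does apply to comprehension, the 85% power figure was computed at a level five times larger than the one that will be used.

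**Working it through.** **1. The stated level.** Bonferroni level = .05/k.

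| Set of tests | k | .05/k |
|---|---|---|
| Usefulness + comprehension | 5 | .0100 |
| Likert items | 6 | .0083 |
| Eight measures under the primary heading | 8 | .00625 |
| Three pairs within one measure | 3 | .0167 |
| Eight measures × three pairs | 24 | .0021 |

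The .01 is reproduced exactly by k = 5, the set in the sensitivity text, and by none of the other sets.

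**2. Family-wise error under each reading.** Assume no true differences, independent outcomes, and Kruskal-Wallis as the gate at the same level. The error is 1 − ∏(1 − αᵢ).

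- Five at .01: 1 − .99⁵ = 4.9%
- Six at .01: 1 − .99⁶ = 5.9%
- Eight at .01: 1 − .99⁸ = 7.7%
- Six at .01 and two comprehension scores at .05: 1 − .99⁶ × .95² = 15.0%

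A null simulation (three arms of 110, 5-point items, 4,000 runs) agrees and shows the effect of correlation and of the gate:

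| Reading | Gated, corr. 0 | Gated, corr. 0.3 | Ungated, corr. 0 |
|---|---|---|---|
| Five at .01 | 4.8% | 4.4% | 13.1% |
| Six at .01 | 5.4% | 4.7% | 14.6% |
| Eight at .01 | 7.5% | 6.7% | 20.4% |
| Six at .01 + two at .05 | 14.4% | 13.3% | 33.7% |

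**3. Why a fixed .01 with a gate is enough for five measures.** Take one measure and three arms. If all arms are equal, an error requires the Kruskal-Wallis test to pass, which has probability .01. If exactly one pair is equal, only that Mann-Whitney test can err, again at .01. If all arms differ, no null is left. Each measure therefore contributes at most .01, and five contribute at most 5 × .01 = .05.

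**4. Power for comprehension at .01.** The SD is not in the protocol, so it is back-solved from the stated power with the normal approximation:

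SD = 0.5 / [(1.960 + 1.036) × √(2/100)] = 0.5 / 0.4238 = 1.18 (1.17 with the t distribution).

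This is an upper limit, because the text says at least 85%. Power = Φ(0.5 / (SD × √(2/n)) − 2.576):

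- SD 1.18, n = 100: Φ(2.996 − 2.576) = Φ(0.42) = 66%
- SD 1.18, n = 110 (330/3): Φ(3.143 − 2.576) = Φ(0.57) = 71%
- SD 1.0 (assumed), n = 100: Φ(3.536 − 2.576) = Φ(0.96) = 83%; the same SD gives 94% at .05

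These figures treat the comparison as a difference in means. They approximate the planned rank test and do not include the gate.

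**The case against.** The best defence is that .01 is simply .05/5 for usefulness and comprehension. The study title and the first research question name the same two domains, so the three-domain primary heading looks like the outlier. The two comprehension scores are bounded counts analysed by rank tests and could be what ordinal was meant to cover. The order of tests reads most naturally as a gate. On that reading the error rate is 4.9% and nothing is uncontrolled. The .05 in the power statement is a planning value and does not fix the test level.

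Most of this stands, and it rules out three stronger conclusions that a reader might draw:

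- *The .01 matches no count of tests.* It matches five.
- *Comprehension is left outside the correction.* The protocol does not say so; this is an inference from the ordinal label and the .05 in the power statement.
- *The error rate exceeds 5%.* That is conditional. Six items at .01 pass 5% only slightly if independent (5.9%) and fall below it at correlation 0.3 (4.7%). The larger figures need eight measures in the family, comprehension tested at .05, or ungated pairwise tests.

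The defence does not settle the text, however. It needs the reader to set aside three measures listed under the primary heading, to read ordinal variables as three of the six Likert items plus two count scores, and to suppose a gate that is not stated. Even then it leaves the power figure at a different level from the test.

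**Conclusion.** The point holds as an internal inconsistency on the primary claims. The protocol gives two primary sets (eight and five measures), a level that fits only the five, a label that does not describe those five cleanly, and a power calculation at another level. For independent outcomes with a Kruskal-Wallis gate, the readings span 4.9% to 15.0% family-wise error. Without a gate the simulated span is 13.1% to 33.7%. Positive correlation lowers all of these.

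The power mismatch arises on the benign reading itself. If .01 governs comprehension, power at 100 per arm is about 66% with the back-solved SD and about 83% with an assumed SD of 1.0. The true figure depends on the pilot variance, which the protocol does not give.

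**What to change.** 1. Name one primary family: the three usefulness items and the two comprehension scores. Move the three perception items to secondary, in both the Primary outcome and the Analyses paragraphs.
2. Replace the ordinal wording with a fixed level of .01 (= .05/5) for each of the five Kruskal-Wallis tests.
3. State the gate: the Mann-Whitney tests for a measure are run at .01 only if that measure's Kruskal-Wallis test is significant at .01. No further pairwise split is needed.
4. Do not let the pairwise level rise in Holm steps. A measure can truly pass its gate while one of its pairs is equal, and that pair still carries error as the later levels relax. The levels sum to .01 + .0125 + .0167 + .025 + .05 = .114. In simulation (five independent 5-point measures, 110 per arm, one arm shifted on three to five of them by 0.5 or 0.8 latent SD, 3,000 runs per setting), rising levels gave about 8% to 10% family-wise error, and a fixed .01 gave about 5%.
5. Restate the comprehension power at .01 and give the pilot SD.

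The cost is a rewording of the outcome and analysis paragraphs and of the power sentence. The perception items lose primary status, and the stated power becomes less favourable.

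### The stated power of at least 85% is for one uncorrected two-group test; it covers neither a Kruskal-Wallis precondition nor the Bonferroni correction in the planned analysis

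*Protocol*

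**What the plan says.** All references are to the protocol.

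- **Sample-size paragraph, section 6.0.** "Based on response variance in our pilot study, a sample size of 100" "participants per condition will yield statistical power with at least 85"%. The effect is given as the "chance of detecting a 0.5-point difference in comprehension (with a" range 0 to 7, for FDA PMI against the "Vendor PMI* group, assuming a two-sided" alpha of .05. No SD is printed.
- **Analyses paragraph, section 6.0.** Outcomes are compared across formats "first with a Kruskal-Wallis test for mean differences, followed by a Mann"-Whitney test for the pairs. A Bonferroni "correction to account for multiple comparisons" follows, with alpha .01 for ordinal variables. The paragraph gives an order of tests. It does not say that the second depends on the first, which alpha Kruskal-Wallis uses, or whether the .01 covers the comprehension score.
- **Section 3.0.** The primary questions are two named pairs. One is "How does the proposed one-page *FDA PMI* compare with the current drug information insert (*Vendor PMI*) in terms of usefulness and comprehension"; the other sets FDA PMI against Decision Critical PMI.
- **Hypotheses, section 6.0.** Both new formats are expected to beat Vendor PMI on comprehension. Their order relative to each other is not stated.

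**The concern.** The power statement describes one two-group comparison at an uncorrected .05. The planned analysis brings in a third arm, an omnibus test and a multiplicity correction, and the power statement accounts for none of them.

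If Kruskal-Wallis is a precondition, a FDA-versus-Vendor difference can be declared only when both tests reject. Power then depends on where Decision Critical PMI scores. If the correction applies to the comprehension score, power falls for that reason as well.

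What is at stake is how a null result is read. A reader would set it against a sensitivity of at least 85%, which the analysis as run may not have. A precondition could also block a contrast that section 3.0 names as primary and that its own pairwise test would have detected.

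**Working it through.** **Inputs from the protocol:** 100 per arm, difference 0.5, two-sided .05, power at least 85%, three arms allocated 1:1:1.

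**Assumptions:** the SD, because none is given; and a rank-test efficiency of .955 relative to the z-test.

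**1. The plan's own figure.** For exactly 85% by a two-group z-test, the standardized difference is (1.960 + 1.036) × √(2/100) = 0.424, so SD = 0.5/0.424 = 1.18. If the 85% was already a Mann-Whitney figure, SD = 1.18 × √.955 = 1.15. The claim is therefore attainable as a two-group calculation, but it cannot be checked without the pilot SD.

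**2. Mann-Whitney alone.** Power = Φ(0.5√.955 / (SD√(2/100)) − z).
- SD 1.18: the first term is 0.4886/0.1669 = 2.93. Power is Φ(2.93 − 1.96) = 83% at .05 and Φ(2.93 − 2.576) = 64% at .01.
- SD 1.15: the first term is 0.4886/0.1626 = 3.00. Power is 85% at .05 and 67% at .01.

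**3. Both tests required.** Three arm means were simulated (1,000,000 draws, 100 per arm). Kruskal-Wallis was taken as the between-group sum of squares against chi-square on 2 df, and Mann-Whitney as a two-sided z. In each cell the first figure is for SD 1.18 and the second for SD 1.15.

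| Rule | Decision Critical midway | Level with either arm | 0.25 above FDA PMI |
|---|---|---|---|
| Mann-Whitney alone, .05 | 83 / 85% | 83 / 85% | 83 / 85% |
| Both at .05 | 74 / 76% | 80 / 82% | 83 / 85% |
| Mann-Whitney alone, .01 | 64 / 67% | 64 / 67% | 64 / 67% |
| Kruskal-Wallis .05, Mann-Whitney .01 | 64 / 67% | 64 / 67% | 64 / 67% |
| Both at .01 | 51 / 54% | 59 / 62% | 64 / 66% |

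Simulation with the actual rank tests (10,000 trials, continuous scores and scores rounded to 0-7) agrees for both at .05. Midway it gives 73-74% (SD 1.18) or 75-76% (SD 1.15), and level it gives 79-80% or 81-82%.

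**4. Why rows three and four match.** With equal arms, and in the normal approximation, the 2-df statistic is never smaller than the squared pairwise z. Rejecting at .01 needs z² > 6.63, which already exceeds the .05 Kruskal-Wallis cut-off of 5.99.

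**5. Intermediate alpha.** At .05/2 = .025, Mann-Whitney alone gives 75 / 78%, and a Kruskal-Wallis precondition at .05 costs 0 to 3 points.

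**6. Sensitivity.**
- SD 1.10 (two-group z-test power 89.5%): both at .05 gives 80% midway and 86% level; Mann-Whitney alone at .01 gives 71%.
- 110 per arm (330/3, no exclusions): both at .05 gives 78-80% midway and 83-85% level. If 10% are excluded as fast completers, 330 × 0.9 = 297, or 99 per arm, so 100 is a fair base.

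**The case against.** The strongest reply is that the sample-size paragraph openly labels a two-group calculation at .05. That calculation is attainable, and powering a key contrast rather than the omnibus test is common practice. All of this stands: the sum itself is not wrong.

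Four stronger readings are tempting, and the protocol does not support them.

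- **That the pairwise tests are conditional on Kruskal-Wallis.** The text gives an order and no condition. The usual reading of such a sequence is conditional, but without that condition power at .05 stays at about 83-85% for the assumed SDs.
- **That true power is 74-80%.** The SD is assumed, and at least 85% is a floor. A smaller pilot SD raises every figure. The midway case is also not the protocol's stated expectation: both new formats are expected to beat Vendor PMI, and Decision Critical PMI level with or above FDA PMI fits that equally well.
- **That the whole drop comes from the omnibus step.** With SD 1.18, about 2 points come from using Mann-Whitney instead of the z-test. At .05 the omnibus step alone costs about 3 points when Decision Critical PMI is level with either arm and about 9 to 10 when it is midway.
- **That dropping the omnibus step would recover 3 to 10 points.** That holds only if both tests are run at uncorrected .05. With Kruskal-Wallis at .05 and a corrected pairwise alpha, the step costs 0 to 3 points at .025 and nothing at .01. It binds hard only if both tests are held to .01.

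Whether the second step is conditional could be settled in a statistical analysis plan. The protocol, however, itself states both the test sequence and a power figure, and the figure does not describe that sequence.

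**Conclusion.** The point holds as a mismatch between the stated power and the stated analysis. At the SD implied by 85%, the printed figure holds only if there is neither a precondition nor a correction.

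The size depends on choices the protocol leaves open. For 100 per arm, SD 1.15-1.18 and rank-test efficiency .955:

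- both tests at .05: about 74-76% (midway) or 80-82% (level), with almost no loss from the precondition if Decision Critical PMI is 0.25 above FDA PMI;
- pairwise test at .01, with no precondition or with Kruskal-Wallis at .05: about 64-67%;
- both at .01: about 51-62% for the midway and level cases.

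The loss from the correction is larger than the loss from a precondition at .05. This is worth correcting before analysis, with medium confidence because neither the SD nor the conditional rule is stated.

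**What to change.** In the Analyses paragraph of section 6.0, state that the two contrasts named in section 3.0 (FDA PMI against Vendor PMI, and FDA PMI against Decision Critical PMI) are tested directly by Mann-Whitney at the corrected alpha, whatever the Kruskal-Wallis result. Report Kruskal-Wallis as supportive.

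In the sample-size paragraph, restate the power at 100 per arm for the rule and alpha actually used, and show the pilot SD. If Kruskal-Wallis is kept as a precondition, give its alpha and the assumed Decision Critical mean as well.

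The cost is a sentence or two in each paragraph and no extra participants. The stated power will probably be less favourable, and error control will rest on the Bonferroni correction alone, which must therefore count the contrasts tested.
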